#### **10.4 Interim Analysis**

No interim analysis is planned.

#### **10.5 Subject Accountability**

The number of subjects in the study will be summarized, both overall and by study center. The number of subjects in each of the Safety, ITT and PP populations will be summarized. In addition, the number of subjects who discontinued ART at Visit 5, and re-started ART at Visit 9 will also be summarized. Any subjects who discontinued/re-started ART at different scheduled visits will be described. In addition, the number of subjects completing / not-completing the final follow-up Visit 10 (end of study) assessment will be summarized along with the primary reason for early withdrawal from the study.

##### **10.5.1 Protocol Deviations**

Subject data will be reviewed for major protocol deviations by a qualified clinical reviewer at a data review meeting to be held prior to database lock. Subjects with any major protocol deviations will be excluded from the PP population. Protocol deviations will be listed by subject.

##### **10.5.2 Subgroup Analyses**

For the reporting of efficacy endpoints subgroup analyses will be performed. The definition of subgroups (either certain subjects excluded or part of their data excluded) will be based on the timing of when a subject is on or off ART during their participation in the study. This will be further documented within the Statistical Analysis Plan.

#### **10.6 Statistical Methods**

In general continuous variables will be described using number of observations (n), mean, standard deviation (SD), geometric mean, minimum, maximum, median, and quartiles. Categorical data will be presented using counts (n) and percentages (%).

All statistical analyses will be performed using appropriate procedures in SAS Software Version 9.2 or higher. Significance of effects will be determined by two-sided tests with p-value < 0.05.

All analyses will be carried out after all participants have completed Visit 10 (or early withdrawal from study) and the study database has been authorized by the Sponsor as complete and final, and protocol deviations have been identified.

##### **10.6.1 Analysis of Demographic and Subject Characteristics**

Descriptive statistics of the demographic profile, baseline conditions, and subject disposition will be summarized.

## **10.6.2 Efficacy Analysis**

### **10.6.2.1 Primary Efficacy Endpoints**

The primary efficacy endpoint of this study is the comparison of the re-boost viral load set-point (definition given in Section 2.2.1.1) after re-boosting and a 16 week ART-free period with the viral load set-point (definition given in Section 2.2.1.1) reported in the initial CT-BI Vacc-4x 2007/1 study (EudraCT Number 2007-006302-13). The primary comparison will be a Wilcoxon signed rank test comparing changes in viral load between the two stated comparison values. The re-boost viral load set-point will also be compared to the pre-ART viral load value, if available from the study CT-BI Vacc-4x 2007/1.

Note: For the reporting of this viral load endpoint, viral load values may have an appropriate transformation (e.g. log base 10) applied prior to endpoint derivation and subsequent analysis.

The co-primary endpoint of this study is the T-cell response (binary outcome: response Yes/No) to Vacc-4x and/or p24 which will be measured by ELISPOT as well as by T-cell proliferative response assay (flow cytometry) and intracellular cytokine staining at Visit 2 (before re-boosting), Visit 4 (two weeks after re-boosting), Visit 6, 9 and 10 (End of Study). These responses will be compared to the T-cell response reported in the initial study CT-BI Vacc-4x 2007/1 (EudraCT Number 2007-006302-13) using McNemar's test. Definition of positive responses will be defined in the statistical analysis plan (SAP).

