## **2 STUDY OBJECTIVES AND ENDPOINTS**

### **2.1 Study Objectives**

#### **2.1.1 Primary Objective**

The primary objective of this study is to evaluate if a re-boost with Vacc-4x could

a) reduce the viral load set-point, and

b) increase the immune response obtained following immunization with Vacc-4x in Study CT-BI Vacc-4x 2007/1 (EudraCT Number 2007-006302-13).

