### **7.2.5 T-cell Response**

Blood samples (approximately 60 mL) will be drawn and the peripheral blood lymphocytes (PBL) separated at each clinical trial site. The PBL will be frozen at  $< -70^\circ\text{C}$  and shipped frozen within 21 days of collection to the central laboratory in Europe (Lausanne, Switzerland) for evaluation. Handling of samples at the site will be detailed in laboratory manuals. The T-cell response to the p24 antigen (including Vacc-4x peptides) will be measured using an ELISPOT test, T-cell proliferation and intracellular cytokine staining at Visit 2, 4, 6, 9 and 10 (End of Study).

ELISPOT is a sensitive immunoassay that will enable detection of antigen-specific T-cells generated after Vacc-4x re-boosting compared with Visit 2 (before re-boosting).

Blood samples will also be analyzed by flow cytometry. Collected cells will be labeled with fluorescent dye (carboxyfluorescein succinimidyl ester [CFSE]), and upon antigen-challenge, activity (intracellular cytokines/ biomarkers, proliferation, T-cell receptor repertoire, surface activation markers) of antigen-specific cells will be visualized and quantified.

T-cell proliferative responses will be evaluated using the T-cell proliferation assay modeled after a previously reported assay ([Kvale, 2005](#)). T-cell proliferative responses will be compared with data reported in the initial study CT-BI Vacc-4x 2007/1 (EudraCT Number 2007-006302-13).

Results for intracellular cytokine testing will be presented in a single written report appended to the Clinical Study Report, to be prepared by the central laboratories. These outputs will be supplied directly to the Sponsor.

In addition, supernatant from the T-cell proliferation assay will be collected for further possible biomarker (e.g., cytokines) testing by Bionor Immuno AS in order to depict Vacc-4x induced T-cell responses. A single written report appended to the Clinical Study Report will be performed by Bionor Immuno AS.

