## **10 STATISTICAL METHODS AND PLANNED ANALYSES**

### **10.1 Determination of Sample Size**

Eighty-eight subjects completed the initial study CT-BI Vacc-4x 2007/1 (EudraCT Number 2007-006302-13) immunization regimen with active Vacc-4x and stopped ART at Week 28. It is estimated that approximately 30 to 40 of these subjects will be eligible for this follow-up, re-boosting study.

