### **10.6.2.2 Secondary Efficacy Endpoints**

The following endpoints (based on continuous data types) will be compared (for within subject comparisons) using the Wilcoxon signed rank test:

- CD4 counts at all visits, absolute numbers, and treatment emergent changes from the mean of Screening and Visit 2 data.
- Change (and percent change) in CD4 count from Visit 5 (discontinue ART) to Visit 6, 7, 8, 9 and 10 (End of Study).
- CD8 counts at all visits, absolute numbers, and treatment emergent changes from the mean of Screening and Visit 2 data.
- Change (and percent change) in CD8 count from Visit 5 (discontinue ART) to Visit 6, 7, 8, 9 and 10 (End of Study).

For each individual subject both the absolute and relative changes in CD4 and CD8 values registered at Visit 9) will be compared with the corresponding values registered at Week 28 (ART discontinued) and Week 52 (or last visit before ART re-initiation) in the initial study CT-BI Vacc-4x 2007/1 (EudraCT Number 2007-006302-13).

- DTH (both induration and erythema) at Visit 2 and Visit 4, in terms of observed areas (mm^2 length x height), areas at Visit 2 will be compared with the corresponding values registered at Visit 4. In addition the values for these DTH parameters at Visit 4 will be compared with the DTH responses reported at Week 18 in the initial study CT-BI Vacc-4x 2007/1 (EudraCT Number 2007-006302-13).

The following endpoints (based on binary data types) will be compared (for within subject comparisons) using McNemar's test:

- DTH (both induration and erythema) at Visit 2 and Visit 4, in terms of a positive test, defined as an area  $\geq 10\text{mm}^2$ . The number of positive tests registered at Visit 2 will be compared with the corresponding values registered at Visit 4. In addition the values for these DTH parameters at Visit 4 will be compared with the DTH responses reported at Week 18 in the initial study CT-BI Vacc-4x 2007/1 (EudraCT Number 2007-006302-13).

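### The only named co-primary T-cell test is McNemar on response yes/no, so it can show conversion of earlier non-responders but not a stronger response in subjects who already responded

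*Protocol*

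**What the plan says.** Protocol Section 2.1.1 gives as primary objective (b) to "increase the immune response obtained following immunization with Vacc-4x in Study CT-BI Vacc-4x 2007/1". Section 10.6.2.1 turns this into a co-primary endpoint, "the T-cell response (binary outcome: response Yes/No) to Vacc-4x and/or p24", measured by ELISPOT, a proliferation assay and intracellular cytokine staining at Visits 2, 4, 6, 9 and 10. The analysis is one sentence: "These responses will be compared to the T-cell response reported in the initial study CT-BI Vacc-4x 2007/1 (EudraCT Number 2007-006302-13) using McNemar's test". The synopsis also names McNemar's test. Only the definition of a positive response is left to the SAP. The scale, the comparator and the test are fixed in the protocol.

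Other sections show that more was available:

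- Section 7.2.5 says that antigen-specific cells will be quantified, and describes ELISPOT as detecting cells generated after re-boosting "compared with Visit 2 (before re-boosting").
- Section 10.6.2.2 treats DTH, a secondary endpoint, on both scales. For area, by signed-rank test, "areas at Visit 2 will be compared with the corresponding values registered at Visit 4". DTH positivity is tested by McNemar. Both are also compared with Week 18 of the earlier study.

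On error and size, Section 10.6 states: "Significance of effects will be determined by two-sided tests with p-value < 0.05". Section 10.1 sets the number by availability: "It is estimated that approximately 30 to 40 of these subjects will be eligible for this follow-up, re-boosting study". No power or effect size is stated.

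**The concern.** Objective (b) is worded as an increase, and everyone enrolled has completed active Vacc-4x immunization, so some will already have responded in 2007/1. Strengthening an existing response is a main purpose of a re-boost. On a yes/no scale such a subject can only stay the same or be lost. The one test named for the co-primary endpoint therefore gives no credit for the effect that the study is designed to produce in these subjects. The sample cannot readily be enlarged to make up for it, because only former participants qualify. A less important endpoint, DTH, is given the magnitude test and the within-study comparison that the co-primary endpoint lacks.

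**Working it through.** **No figure to reproduce.** The protocol gives no power calculation for this endpoint. The check asks what the named test can and cannot detect.

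**Inputs from the protocol:** two-sided 0.05 (Section 10.6); N = 30 to 40 (Section 10.1). **Assumed:** the exact form of McNemar's test (the protocol does not say which), and a 2007/1 response rate of 45% to 90%. The only ELISPOT responder rate in the protocol is 45%, from the Phase I study (Section 1.4).

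**Step 1. Which subjects count.** Let b be the number changing from no to yes and c the number changing from yes to no. Exact two-sided p = 2 × P(X ≤ min(b, c)), with X ~ Binomial(b + c, 0.5). Yes/yes pairs do not enter. If every prior responder doubled and nobody changed status, b = c = 0 and p = 1.

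**Step 2. What significance for gain needs.**

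- 5 gains, 0 losses: 2 × 0.5^5 = 0.0625
- 6 gains, 0 losses: 2 × 0.5^6 = 0.031
- 8 gains, 1 loss: 2 × (1 + 9)/512 = 0.039 (7 and 1 give 0.070)
- 10 gains, 2 losses: 2 × (1 + 12 + 66)/4096 = 0.039 (9 and 2 give 0.065)

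At least 6 prior non-responders must be in the sample. Significance is impossible above a prior response rate of (30 − 6)/30 = 80% at N = 30, or (40 − 6)/40 = 85% at N = 40.

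**Step 3. Power if the effect is pure conversion.** Assume half of prior non-responders convert and none are lost. Then b ~ Binomial(N, 0.5 × (1 − prior rate)), and power is P(b ≥ 6).

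| Prior rate | N = 30 | N = 40 |
|---|---|---|
| 45% | 0.87 | 0.98 |
| 60% | 0.57 | 0.84 |
| 70% | 0.29 | 0.57 |
| 80% | 0.07 | 0.21 |
| 90% | 0.003 | 0.014 |

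**Step 4. Power if everyone shifts.** Assume a bivariate-normal response, a uniform 0.5 SD shift, within-subject correlation 0.4 to 0.6, and both tests applied to the same pair of measurements (simulation, approximate).

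| Prior rate | N = 30, McNemar | N = 40, McNemar |
|---|---|---|
| 45% | 30-35% | 43-50% |
| 70% | 19-24% | 30-35% |
| 90% | 2-3% | 6% |

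Signed-rank power does not depend on the prior rate: about 65-83% at N = 30 and 78-93% at N = 40.

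**Step 5. Power if only prior responders rise.** Assume a doubling (+0.30 log10) in prior responders only, and an SD of the paired log10 change of 0.4 to 0.6. At N = 30, signed-rank power is 0.35 to 0.19 at a 45% prior rate, 0.73 to 0.43 at 70% and 0.93 to 0.64 at 90%. If no status changes, McNemar has no discordant pairs and p = 1.

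**Step 6. Effect of assay drift on a cross-study magnitude test.** With no vaccine effect, N = 30 and correlation 0.5 (assumed), an upward drift between studies of 0.3 SD makes the signed-rank test falsely significant in about 33-34% of trials. A drift of 0.5 SD does so in about 73-74%. For McNemar the rate is 1-12% under an uncalibrated 0.3 SD drift, and about 1% or less under a 0.5 SD drift if positivity is calibrated within each study.

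**The case against.** Several points on the other side stand.

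- **The binary scale has support.** Section 1.1 reports that positive ELISPOT responses to p24 in the Vacc-4x group went with a lower viral load set point, and reads this as possibly a qualitative rather than a quantitative difference. Responder status is thus linked to the other co-primary endpoint and is not simply discarded information.
- **Objective (b) requires the earlier study as comparator.** Visit 4 against Visit 2 answers a different question, so it can be added but cannot replace that comparison.
- **Magnitude is not wholly ignored.** Section 10.6 provides descriptive summaries of continuous variables, and Section 7.2.5 says that proliferative responses will be compared with the 2007/1 data. A reader might infer that a rise among prior responders would go unseen anywhere in the study. The documents do not support that. What is missing is a specified test of it.
- **A cross-study magnitude test is vulnerable.** Step 6 shows that it would turn assay drift into apparent effect.
- **The powers depend on the assumed alternative.** A uniform shift with no assay floor favours signed-rank. Treating sub-threshold values as background lowers its power at a 45% prior rate (N = 30) to 52-66%, with McNemar at 29-34%. The 45% comes from 11 Phase I subjects given 0.4 mg. An uncorrected asymptotic McNemar test would need fewer discordant pairs.

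None of this changes Step 1. With one common cut-off in both studies, wherever the SAP puts it, yes/yes pairs drop out.

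**Conclusion.** The point holds in a limited form. The co-primary analysis as fixed can show that more subjects respond than before, but cannot show that the response rose in those who already responded, although the objective is an increase and the assays yield quantities. This follows from the test itself and needs no assumed rate.

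The size does rest on assumptions. At N = 30 and 45% prior response, a uniform 0.5 SD shift gives about 30-35% power for McNemar against 65-82% for signed-rank. The gap widens as the prior response rate rises. Where the effect is mainly conversion, McNemar does well at a low prior rate (87% at 45%).

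Two stronger readings are tempting and not supported. One is that the endpoint cannot address objective (b) at all: it can, through conversion. The other is that the McNemar comparison should be replaced by a quantitative comparison with 2007/1: drift between studies would make that unsafe as a primary test.

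**What to change.** In Section 10.6.2.1 and the synopsis:

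1. Add a pre-specified paired Wilcoxon signed-rank test on the log-transformed quantitative T-cell response for one named assay and antigen (for example ELISPOT to p24), Visit 4 against Visit 2, as the within-study test of the re-boost effect. This mirrors the DTH analysis.
2. Keep the McNemar comparison with 2007/1 for objective (b).
3. Add a quantitative comparison with the 2007/1 values as supportive only, and only where subject-level values from a comparable assay exist. The protocol speaks only of responses reported there.
4. State which T-cell test is the co-primary one, so that the added test does not create uncontrolled multiplicity.
5. While editing, align the synopsis statistical text, which lists Visit 5 where Section 10.6.2.1 and Table 1 have Visit 4.

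The cost is wording and one extra within-study analysis; the Visit 2 and Visit 4 samples are already scheduled. The limitation to accept is that the Visit 2 comparison measures the re-boost against the pre-boost level, not against the earlier peak. Its power depends on a shift and a correlation that the protocol does not give.

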| Statistical Methods: | 
All subjects who receive at least one re-boosting immunization will be included within the safety population. All safety analyses will be conducted on the safety population. All subjects who receive at least one re-boosting immunization and have any post-baseline efficacy data will be included in the ITT population. Unless otherwise indicated, all efficacy analyses will be conducted on the ITT Population. All ITT subjects who receive two re-boosting immunizations discontinue ART at Week 13 (as planned) and who do not incur a major protocol violation that would challenge the validity of their data will be included within the PP population. All efficacy analyses will also be conducted on the PP population. No interim analysis is planned.
 
In general continuous variables will be described using number of observations (n), mean, standard deviation (SD), geometric mean, minimum, maximum, median, and quartiles. Categorical data will be presented using counts (n) and percentages (%). All statistical analyses will be performed using appropriate procedures in SAS Software Version 9.2 or higher. Significance of effects will be determined by two-sided tests with p-value < 0.05.
 
All analyses will be carried out after all participants have completed Visit 10 (or early withdrawal from study) and the study database has been authorized by the Sponsor as complete and final, and protocol deviations have been identified.
 
The primary efficacy endpoint of this study is the comparison of the re-boost viral load set-point after re-boosting and a 16 week ART-free period with the viral load set-point reported in the initial CT-BI Vacc-4x 2007/1 study (EudraCT Number 2007-006302-13). The primary comparison will be a Wilcoxon signed rank test comparing changes in viral load between the two stated comparison values. The re-boost viral load set-point will also be compared to the pre-ART viral load value, if available from the study CT-BI Vacc-4x 2007/1. The co-primary endpoint of this study is the T-cell response to Vacc-4x and/or p24 which will be measured by ELISPOT as well as by T-cell proliferative response assay (flow cytometry) and intracellular cytokine staining at Visit 2 (before re-boosting), Visit 5 (two weeks after re-boosting), Visit 6, 9 and 10 (End of Study). These responses will be compared to the T-cell response reported in the initial study CT-BI Vacc-4x 2007/1 (EudraCT Number 2007-006302-13) using McNemar's
 |

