## **1.6 Potential Risks and Benefits**

Participants will provide important scientific information that may contribute to improved future vaccination of HIV-positive subjects. Potential benefits for participants include a possible sustained improvement in the immune response to p24 and HIV. Potential risks include the discomfort and inconvenience associated with the immunizations and the risk of known or unknown side effects of exposure to Vacc-4x and Leukine® including, most commonly, local reactions at the site of injections and fatigue (incidence not yet determined). However, since all subjects in this study have participated in Study CT-BI Vacc-4x 2007/1 (EudraCT Number 2007-006302-13) they are aware of potential discomfort.

Interruption of ART for extended periods is associated with an increased morbidity and mortality, thus planned long-term therapy interruption strategies are not recommended outside of controlled clinical trials (Department of Health and Human Services [DHHS] Guidelines for the Use of Antiretroviral Agents in HIV-infected Adults and Adolescents, January 29, 2008). In the present study the subjects are stopping ART for a relatively short period of up to 16 weeks, during which they will be closely monitored.

The subjects will remain on ART throughout the immunization period and for another 10 weeks after the final immunization, in order to prevent interference from the immune response caused by viral rebound associated with ART interruption. In all studies with Vacc-4x, subjects have been vaccinated when on ART with no loss of viral control. Viral rebound was only observed after subjects stopped ART. During the ART interruption period, subjects are being monitored carefully and ART will be restarted if subjects exceed pre-specified criteria for viral load and CD4 reduction or for any other medical reasons (4.4.1.3 Criteria for Restart of ART).

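### The co-primary T-cell endpoint covers three assays, one or two antigens and five visits at an unadjusted 0.05, with no deciding test, no reference visit and no rule for combining it with viral load

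*Protocol*

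**What the plan says.** Section 10.6.2.1 states: "The co-primary endpoint of this study is the T-cell response (binary outcome: response Yes/No) to Vacc-4x and/or p24". Three assays are used (ELISPOT, flow-cytometric proliferation and staining for intracellular cytokines), and the sampling times are listed as "Visit 2 (before re-boosting), Visit 4 (two weeks after re-boosting), Visit 6, 9 and 10 (End of Study"). The comparison is historical and uses McNemar's test: "These responses will be compared to the T-cell response reported in the initial study CT-BI Vacc-4x 2007/1". Section 2.2.1.1 and the synopsis endpoint list give the same assays and visits as a primary endpoint.

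The only threshold is the general one in Section 10.6: "Significance of effects will be determined by two-sided tests with p-value < 0.05". Section 10.6.2.1 leaves one T-cell item to the SAP, the definition of a positive response. It does not say which assay, antigen or visit decides, which visit of the initial study is the reference, or how the T-cell and viral load co-primaries combine.

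On timing, Table 1 places T-cell sampling at Visits 2, 4, 6, 9 and 10, with the planned ART stop at Visit 5 and re-start at Visit 9. Section 1.6 explains why ART continues after the last immunization: "in order to prevent interference from the immune response caused by viral rebound associated with ART interruption". In the synopsis, the statistical methods entry gives the first post-boost T-cell sample as "Visit 5 (two weeks after re-boosting").

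**The concern.** Primary objective (b) asks whether the re-boost increases the immune response obtained in the initial study. As written, the endpoint for it is a grid of possible McNemar tests, each judged at 0.05. With no deciding test, a report could point to any favourable cell as a positive co-primary result, and the false-positive rate of such a claim is well above the nominal one.

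The cells also answer different questions. Visit 2 is sampled before the boost and can show only persistence from the initial study. Visits 6 and 9 are sampled after the planned ART stop, when by Section 1.6 viral rebound can itself affect the immune response. The study is open and single-arm, so no concurrent control separates the two influences. The choice of initial-study reference visit then matters a great deal, and it is left open.

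**Working it through.** **Plan's own figure.** There is none to reproduce. The 30 to 40 subjects in Section 10.1 are an eligibility estimate, and no power or familywise error rate is stated.

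**Number of tests** (inputs from Section 10.6.2.1: 3 assays, 2 antigens, 5 visits).
- All visits: 3 × 2 × 5 = 30.
- Without pre-boost Visit 2: 3 × 2 × 4 = 24.
- Post-boost, antigens merged into one response: 3 × 1 × 4 = 12.

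The post-boost range of 12 to 24 bears on objective (b).

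**At least one p < 0.05 under no effect, independent tests:** 1 − 0.95^k.
- k = 12: 1 − 0.95^12 = 46%.
- k = 24: 1 − 0.95^24 = 71%.

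**Correlated tests.** The tests share subjects, so independence gives an upper figure. The correlation ρ is not in the protocol; I assume equicorrelated normal statistics. With z = 1.96 and g the shared normal factor, the chance is

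1 − ∫ φ(g) [Φ((z − √ρ g)/√(1−ρ)) − Φ((−z − √ρ g)/√(1−ρ))]^k dg.

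For favourable results only, the second Φ term is dropped.

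| ρ (assumed) | Either direction, k = 12 | Either direction, k = 24 | Favourable only, k = 12 | Favourable only, k = 24 |
|---|---|---|---|---|
| 0 | 46% | 71% | 26% | 46% |
| 0.3 | 40% | 59% | 20% | 31% |
| 0.5 | 32% | 46% | 16% | 23% |
| 0.7 | 23% | 31% | 12% | 16% |
| 0.9 | 13% | 16% | 7% | 8% |

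A single test gives 5% in either direction and 2.5% in the favourable one.

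**Exact McNemar.** The exact test is conservative at this size. With n = 30 to 40 and an assumed discordance of 0.2 to 0.4, its attained two-sided size is 0.0128 to 0.0285. Favourable only, with independent tests:
- k = 12: 1 − (1 − 0.0128/2)^12 = 7%, up to 1 − (1 − 0.0285/2)^12 = 16%.
- k = 24: 1 − (1 − 0.0128/2)^24 = 14%, up to 1 − (1 − 0.0285/2)^24 = 29%.

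Correlation would lower these again. The asymptotic test keeps close to its nominal size (0.043 to 0.049 in the same scenarios). The protocol does not say which version applies.

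**Timing** (days from Table 1).
- Visit 4 is day 28, which is 28 − 15 = 13 days after the second boost. It is the only post-boost T-cell sample before the planned ART stop at Visit 5 (day 84).
- Visit 6: 112 − 84 = 28 days after the Visit 5 date. Visit 9: 196 − 84 = 112 days. Both lie in the ART-free period for subjects who stop.
- Visit 10: 252 − 196 = 56 days after the visit at which re-start is recommended.
- Visit 5 is 84 − 15 = 69 days after the second boost, so it is not two weeks after it. Neither Table 1 nor Section 6.3.2.4 schedules a T-cell sample there.

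**The case against.** **The SAP may settle it.** Assay hierarchy and multiplicity often sit in the SAP, and this one is not shown. The study is also small, open and phase II, with no power claim. That tempers the severity. But the protocol itself fixes the co-primary endpoint, its visits and the threshold, and defers only the definition of a positive response. It can be specific elsewhere: Section 10.6.2.2 ties DTH to Week 18 and CD4 and CD8 to Weeks 28 and 52 of the initial study.

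**No text says one significant test is enough.** True: the assays are joined conjunctively, and a rule requiring every test to succeed would not inflate the error. No such rule is stated either. Objective (a) and (b) could likewise be read as requiring both co-primaries, in which case the viral load test adds no inflation. Section 7.2.5 treats the peptides as part of the p24 antigen, which favours 12 tests over 24.

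**A chance finding is not shown to be likely.** A reader might infer from 71% that a false positive is more probable than not. That figure assumes independence, two antigens and either direction. Under the more realistic settings above, the favourable-only chance is well below one half.

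**Rebound confounding is possible, not established.** A reader might infer that the study cannot attribute any T-cell response to the re-boost, or that all three late visits reflect rebound. The documents do not support this. The initial study also stopped ART, so an off-ART visit compared with an off-ART visit would have viremia on both sides. Visit 10 comes eight weeks after recommended re-start, so the concern applies mainly to Visits 6 and 9. Nor is Visit 4 the only on-ART sample: subjects who re-start are on ART at Visit 10, those who fail the Visit 5 criteria remain on it at Visits 6 and 9, and subjects may enter the study off ART.

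**Cytokine results in an appended report.** Section 7.2.5 says: "Results for intracellular cytokine testing will be presented in a single written report appended to the Clinical Study Report". One might infer that this assay has left the co-primary analysis. The text supports only a point about where results are filed.

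**Conclusion.** The point holds as a defect of definition. The protocol sets a multi-part co-primary endpoint under one unadjusted threshold and names neither a deciding test nor a reference visit nor a combination rule. If any one of 12 to 24 post-boost tests could be claimed, the favourable-only false-positive chance is about 16% to 23% at an assumed correlation of 0.5, instead of 2.5%. It is lower with exact McNemar or stronger correlation, and higher with weaker correlation. Every entry in the table exceeds its single-test value. These sizes rest on the assumed correlation and discordance and on the any-one-test reading, which the text permits but does not state.

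Attribution at Visits 6 and 9 is uncertain unless the comparator is a matched off-ART visit. The Visit 5 entry in the synopsis is a plain error against the sampling schedule. This should be corrected, but it does not invalidate the study.

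**What to change.** In Section 10.6.2.1, with matching text in Section 2.2.1.1 and the synopsis:

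1. Name one deciding T-cell test: one assay, one antigen and one visit. ELISPOT to p24 at Visit 4 is a reasonable example, because Section 1.1 reports a preliminary association between positive p24 ELISPOT responses and a lower viral load set point. It is not the only defensible choice.
2. Name the initial-study visit it is compared with. Without this, the single test is still undefined.
3. State the co-primary rule: either both viral load and T-cell response must succeed at 0.05, or each is tested at 0.025.
4. Make the other assays, antigens and visits secondary or descriptive, and note the possible influence of rebound at Visits 6 and 9.
5. In the synopsis statistical methods, change Visit 5 to Visit 4 for the T-cell sample.

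The cost is wording, plus the loss of any primary claim from other assays or later visits; no data are lost. Under exact McNemar, the smallest all-one-way discordant count that reaches significance is 6 pairs at 0.05 (2 × 0.5^6 = 0.031) and 7 at 0.025 (2 × 0.5^7 = 0.016). Keeping all 24 tests under Bonferroni would need 10 (2 × 0.5^10 = 0.00195, against 0.05/24 = 0.00208), which is demanding with 30 to 40 subjects.
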